#### Health economic assessment

Health economics data will be collected during the study to: (a) assess differences in costs and health-related quality of life based on prognosis risk identified by the BBMs and (b) support the development of a cost-effectiveness model for the early health technology assessment of BBM as a component of diagnosis.

Health-related quality of life will be measured using the EQ-5D-5L instrument at baseline and at the 52-week visit for 20% of the cohort. EQ-5D-5L responses will be converted into health utility values in accordance with National Institute for Health and Care Excellence guidance^52^ and combined with survival data to estimate quality-adjusted life years (QALYs). Participants’ perspectives on diagnostic and biomarker information will be explored through a qualitative question administered at study sites, involving 15–20 participants recruited both from this study and through the READ-OUT PPIE programme.

NHS secondary care resource use and medication data will be obtained through linkage with electronic health records and valued using national cost data. Use of primary care services, social care, productivity losses, informal care and other anticipated resource changes will be captured via self-reported questionnaires at baseline and at the 52-week visit (for the subsample), and similarly valued using national costs.

Differences in costs and EQ-5D-5L utility values by risk group at baseline and throughout the follow-up period will be analysed using generalised linear models. Associations between changes in BBM values (from baseline to the 52-week visit) and both costs and EQ-5D-5L utility values will be assessed using panel regression methods, including fixed and random effects models. Missing data will be handled in line with best practice for cost-effectiveness analyses.^53^ This READ-OUT phase 1 will assess the relationship between BBM results and baseline and longitudinal health-related quality of life assessments. The impact of BBM disclosure on these metrics will be assessed in a second clinical trial phase of READ-OUT.

We will develop economic models to evaluate the early cost-effectiveness of BBM and support their translation into clinical practice. NHS and societal perspectives will be considered, and the primary health outcome will be QALYs. The final economic model structure will be developed in collaboration with clinicians and epidemiologists involved in the study. Diagnostic performance metrics of BBMs will be incorporated directly into the model to link diagnostic accuracy with long-term outcomes and costs. Parameter estimates for the early health technology assessment models will be informed by data from READ-OUT phase 1 and supplemented with evidence from targeted and systematic literature reviews.

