### Participant recruitment and selection

The observational phase of READ-OUT will recruit 3165 participants. Participants are over the age of 45, able to provide blood samples and willing to consent to linkage to NHS health records (box 1). There are no restrictions on diagnosis or severity. People with cognitive symptoms attending secondary care services for dementia and related conditions (‘memory clinics’) are eligible, regardless of the diagnosis emerging from assessment in those services. Participants must provide informed consent, unless the participant does not have capacity for consent to study participation, in which case advice will be sought from a consultee or their guardian/attorney as set out in the relevant legislation in the devolved nations of the UK.

Box 1Inclusion and exclusion criteria for READ-OUT phase 1Inclusion criteriaAged 45 or above.Referred or referable with cognitive or behavioural symptoms and/or diagnosed with a cognition-related disorder; including those with subjective cognitive impairment and functional disorders.Willing and able to give informed consent for participation in the study.ORAdults who otherwise lack the capacity to consent, but for whom advice regarding participation has been obtained via a consultee using the personal consultee process.Exclusion criteriaLack of venous access.Unwilling to consent to NHS data linkage.NHS, National Health Service; READ-OUT, REAl world Dementia OUTcomes.

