### Sample size and power

Given that the assessment of clinical utility of BBMs requires accuracy, READ-OUT prioritises receiver operator characteristics. Diagnostic and prognostic performance metrics are accuracy, sensitivity, specificity and positive- and negative-predictive values. A cohort size of N~3000 allows comparison of tests in subgroups with multiple predictors to detect events (dementia diagnosis, dementia aetiology, prognostication) and greater than 10 events per predictor using unbiased logistic regression, machine learning approaches, and out-of-sample testing.^38 39^ Power for individual tests will vary according to the prevalence of each dementia type in the cohort. Indicative frequentist power calculations were performed in R V.4.4.1 using the *powerMediation*^40^ packages. For example, we assume rates of mild cognitive impairment (MCI) of 17% in line with UK memory clinic^41^ with annual conversion rates from MCI to dementia of 10%–15%.^42 43^ A cohort of N=3165 gives 80% power at 5% significance to detect a change in the probability of converting to dementia within a year from 10% to 15% (an OR of 1.5) when the BBM is increased by 1 SD above the mean.

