#### BBM modelling and validation

The statistical analysis plan is designed to test the READ-OUT phase 1 research questions with tailored approaches incorporating different tiers of BBMs. Outcomes will be reported in line with relevant standards.^49^

For diagnostic modelling, both traditional statistical approaches (eg, logistic regression) and supervised or unsupervised machine learning techniques (eg, Random Forests,^50^ XGBoost,^51^ support vector machines) will be applied to develop and compare models for diagnostic classification. Performance will be evaluated for individual biomarkers, combinations of biomarkers and models integrating biomarkers with demographic and clinical information, accounting for variation across ethnicity and comorbidities. Diagnostic accuracy will be assessed using metrics such as sensitivity, specificity, positive and negative predictive values, and the area under the receiver operating characteristic curve. The NULISA and other platforms will output high-dimensional data, and we will consider internal validation and biomarker ranking, feature selection, and shrinkage and regularisation methods.

Optimal thresholding of model outputs will be informed by insights from the public and patient involvement and engagement (PPIE) arm of the study, recognising the real-world impact of false positives and false negatives.

Prognostic accuracy will be assessed using longitudinal data and linked electronic health records. Model selection will be guided by the data type and number of time points, and will include approaches such as change-from-baseline analysis of health-related quality of life at 1 year, multilevel and generalised additive models for repeated cognitive outcomes, and models that accommodate censored data for survival and longitudinal diagnostic changes. READ-OUT also leverages DPUK studies with gold-standard biomarker testing, including CSF and PET markers.

In relevant subgroups, we will also evaluate the reliability and resilience of the assays. This includes: (a) assessing deliverability and scalability by comparing standard phlebotomy (all participants) with alternative sampling methods, such as postal blood spot cards; (b) examining test–retest reliability using intraclass correlation coefficients, along with evaluating tolerance to processing delays; and (c) comparing performance across both mass spectrometry and other assay platforms.

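### Costs and EQ-5D-5L utility are to be modelled by risk group with no explicit analysis on the continuous BBM or risk level; the lost precision matters chiefly in the 52-week subsample

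*Protocol article*

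**What the plan says.** All references are to the protocol article.

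- *Health economic assessment*, objective (a), is to "assess differences in costs and health-related quality of life based on prognosis risk identified by the BBMs".
- The method named for this is: "Differences in costs and EQ-5D-5L utility values by risk group at baseline and throughout the follow-up period will be analysed using generalised linear models". The number of groups, the cut-points and a power target are not given.
- The next sentence plans panel regression, with fixed and random effects, for "Associations between changes in BBM values (from baseline to the 52-week visit) and both costs and EQ-5D-5L utility values". The exposure there is change in BBM, not its level.
- The same section says that phase 1 "will assess the relationship between BBM results and baseline and longitudinal health-related quality of life assessments". This names no model, does not say whether the BBM is continuous or grouped, and does not mention costs.
- *Sample size and power* contains the only power statement. It concerns conversion from mild cognitive impairment (MCI) to dementia and treats the BBM as continuous: the effect is the change in probability "when the BBM is increased by 1 SD above the mean".
- *BBM modelling and validation* says: "Optimal thresholding of model outputs will be informed by insights from the public and patient involvement and engagement (PPIE) arm of the study".

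**The concern.** Most of the BBMs are assay concentrations, and a predicted prognostic risk is a continuous quantity. Replacing it with a few groups treats everyone within a group as alike and people just either side of a boundary as different. The gradient in costs or utility is then estimated less precisely, and its size depends on where the boundaries fall. The article fixes no boundaries for these risk groups and cites no guideline that requires them.

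The loss is worst where data are scarce. EQ-5D-5L and self-reported resource use (primary care, social care, informal care, productivity) are collected at 52 weeks in 20% of the cohort only. Phase 1 estimates are also to inform the parameters of the economic model, so avoidable imprecision can carry forward.

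**Working it through.** **Inputs from the article.** Cohort 3165; 52-week subsample 20%, so 0.20 × 3165 = 633; 5% significance, taken as two-sided; MCI share 17%; 10% conversion; OR 1.5 per SD.

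**Assumptions, not in the article.** A normal risk score linearly related to the outcome on the analysis scale; group splits and correlations r as shown.

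**1. The plan's own power figure.** For logistic regression on one continuous covariate,

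n = (z₀.₉₇₅ + z₀.₈₀)² / [p(1−p)(ln OR)²] = (1.960 + 0.842)² / [0.10 × 0.90 × (ln 1.5)²] ≈ 531 people with MCI.

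531 / 0.17 ≈ 3124, within 3% of 3165. With 0.17 × 3165 ≈ 538 people with MCI, power is 80.6%. The figure reproduces and rests on a continuous BBM. It says nothing about power for costs or utility.

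**2. Information retained after grouping.** For two groups with upper fraction q and cut c, retained = φ(c)² / [q(1−q)]. At 50:50 this is 0.3989² / 0.25 = 0.637; at 20:80 it is 0.2800² / 0.16 = 0.490. For k groups, sum (φ(lower cut) − φ(upper cut))² / (group share) over the groups.

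**3. Power after grouping, if the continuous analysis had 80%.** For a 1-df test, power = Φ(2.802 × √retained − 1.960). For k groups compared as categories, use a noncentral chi-square on k−1 df with noncentrality 2.802² × retained.

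| Grouping | Retained | Lost | Power, 1-df | Power, k−1 df |
|---|---|---|---|---|
| 50:50 | 0.637 | 36% | 61% | same |
| 30:70 | 0.576 | 42% | 57% | same |
| 20:80 | 0.490 | 51% | 50% | same |
| 10:90 | 0.342 | 66% | 37% | same |
| 3 equal | 0.793 | 21% | 70% | 60% |
| 4 equal | 0.861 | 14% | 74% | 57% |
| 5 equal | 0.897 | 10% | 76% | 54% |

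With three to five groups the cost in power depends on the test. Scored as an ordered trend, the loss is about 4 to 10 points. Compared as unordered categories, the extra degrees of freedom use up the gain in retained information.

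**4. Power at the actual sample sizes.** Power = Φ(atanh(r√retained) × √(n−3) − 1.960), with tertiles scored as a 1-df trend.

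| n | r | Continuous | Tertiles | 50:50 | 20:80 | 10:90 |
|---|---|---|---|---|---|---|
| 633 | 0.10 | 71% | 61% | 52% | 42% | 31% |
| 633 | 0.15 | 97% | 92% | 86% | 75% | 60% |
| 3165 | 0.05 | 80% | 71% | 61% | 50% | 38% |
| 3165 | 0.10 | 99.99% | 99.9% | 99.4% | 97.6% | 90.9% |

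A continuous analysis reaches 80% power at r ≈ 0.11 with 633 people and at r ≈ 0.05 with 3165. At baseline and r = 0.10 or more, grouping therefore costs at most about 9 points, and far less for balanced splits.

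**The case against.** The strongest reply has four parts.

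- **Other analyses exist.** The section also plans panel regression on BBM changes and an analysis of BBM results against quality of life. This stands in part: one cannot say that grouping replaces every continuous analysis. But the first concerns change rather than level, and the second states no form for the BBM and leaves out costs.
- **Coding of the exposure may be in the SAP**, which is not shown. The number of groups and the cut-points may well be there, and their absence from the article is no fault. The choice to compare by risk group, however, is stated in the article.
- **Group means may be what is wanted.** Diagnostic performance metrics enter the economic model directly, and several of these need a thresholded result, so costs and utilities by category are natural inputs. Power is also not the main criterion when estimating parameters. This stands, and it is why group means should be kept.
- **Not every figure applies everywhere.** Linked records supply secondary-care and medication costs, so those follow-up costs are not confined to the 633. Apolipoprotein E status, a Tier 1 test, is not a continuous measure. Both points stand.

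A reader might also infer that the patient-informed thresholds define these risk groups. The article does not say so: that sentence follows the diagnostic-modelling paragraph and concerns false positives and false negatives. Nor does the per-SD power statement contradict the grouped analysis, since it addresses a different outcome.

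**Conclusion.** The point holds in limited form. The article specifies risk-group models for costs and utility and no explicit continuous analysis of BBM or risk level, most clearly for costs. Under a normal score and a linear effect, the information lost is about 10% to 21% with five to three equal groups, and 36% to 66% with two groups split from 50:50 to 10:90.

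A reader might infer a general loss of 20 to 40 points of power. The documents do not support that: it needs two groups (or several groups tested as unordered categories) and a continuous analysis starting near 80% power. Neither the number of groups nor any power for these outcomes is stated. The practical exposure is 52-week utility and self-reported costs in at most 633 people. At baseline it is small unless the association is weaker than about r = 0.10. This is an avoidable loss of precision and does not invalidate the analysis.

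**What to change.** In the same generalised linear models, enter the BBM value or predicted risk as a continuous covariate, per SD on a suitable scale and with a spline for non-linearity. Use that model to test and estimate the gradient in costs and utility. Keep risk-group means, either raw or derived from the fitted model, as inputs to the economic model, and define the groups before the cost and utility data are analysed. A measure that is categorical by nature stays categorical.

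The cost is a change of wording in the analysis plan and slightly more analysis, with no new data; the study is still recruiting. The downside is that a functional form must be chosen, and means derived from the curve depend on it. The spline limits this, and the raw group means provide a check.

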### Public and patient involvement and engagement

The design of READ-OUT was informed by a specialist PPIE group, including those with lived experience of dementia or of attendance at a memory clinic. A further PPIE group has been created to support the project through phases one and two, consisting of people who have attended secondary care memory clinics and individuals from under-represented groups thought to be at risk of dementia.

Viewpoints of the PPIE group will inform issues associated with the study research questions and will feed back to the statistical analysis plan and health economic analysis. A critical element of READ-OUT is understanding whether people want to know their results, what they want to know and how best this information is conveyed. We will use quantitative and qualitative data to design potential ways of conveying information, which we will feed back to our PPIE group to understand the best way of communicating the results of biomarkers and risk. These processes will be reviewed as we collect BBM data in under-represented groups, to ensure they remain as applicable and appropriate as possible.

### Current status

This study is active and currently recruiting (https://clinicaltrials.gov/study/NCT07238049).

## Ethics and dissemination

This study will be conducted in accordance with the principles of the Declaration of Helsinki. READ-OUT has received Research Ethics Committee approval (REC reference 24/WA/0330) and approval through the Health Research Authority/Health and Care Research Wales (IRAS project 342412).

Anonymised READ-OUT study data will be maintained on the Data Portal hosted by DPUK (https://portal.dementiasplatform.uk). Data will be made available with a managed access process through DPUK and subject to a DPUK Data Access Agreement.

Study investigators will publish manuscripts setting out real-world BBM performance in peer-reviewed publications. If multivariate biomarker sets improve performance, the READ-OUT team will develop a simplified scoring-/weighting- system to aid bedside utility. Aggregated study results will be communicated back to participants through newsletters, social media and updates on the study website.
